| Analysis as above repeated examining patients with neuropathic pain only, and other pain types only, and patients who were cannabinoid naïve vs previous cannabinoid users, though these may be underpowered. | Change from baseline to end of week 8 | In a four-week open label study of dronabinol for patients with non-cancer chronic pain (nociceptive, neuropathic, and both), dronabinol was associated with a reduction in pain intensity and pain bothersomeness.^46^  In a study of over 600 patients with multiple sclerosis comparing dronabinol, oral cannabis, and placebo either dronabinol or oral cannabis were both associated with a reduction in pain compared to placebo and dronabinol was associated with fewer adverse effects compared to oral cannabis extract.^47^  Dronabinol may also have a benefit in pain sensitization.  Dronabinol reduces pain unpleasantness in studies of provoked pain, which may be explained by reduced processing between the sensory (pain severity) and limbic (emotional aspects of pain) areas of the brain seen in functional MRI studies.^48,49^ Thus, dronabinol may reduce pain impact by direct analgesic effect of nociceptive or neuropathic pain or by reducing pain sensitization and pain unpleasantness. |

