## 4.2 Scientific Rationale for Study Design

People with sickle cell disease (SCD) have chronic pain from multiple sources^2,3,15^ Inflammation is a driver of pain, end organ damage and early mortality in SCD.^16^ Tetrahydrocannabinol (THC) is a partial agonist for cannabinoid receptors (CB1 and CB2), and has been shown to be effective for the treatment of chronic pain and neuropathic pain in conditions such as cancer and multiple sclerosis.^6,17,18^ There is also evidence from murine models of SCD that CB1 agonists can reduce signs of chronic and neuropathic pain as well as inflammatory cytokines that are important in pain development in SCD.^3,4,19^ The proposed research is built on the scientific premise that dronabinol, an FDA-approved synthetic THC medication may treat chronic pain in SCD and reduce inflammation, and therefore is a promising agent for either the treatment of chronic pain or for treatment of the disease directly through reduction of inflammation.

Randomization will be done 1:1 to dronabinol or placebo in blocks of four, stratified by pain type (neuropathic or not) and past-year cannabinoid use (yes or no). Randomization will be done by the pharmacy. Neuropathic pain will be defined by LANSS score >12. Past-year cannabis use will be defined by self-report of any cannabinoid use (medical, illicit, or cannabidiol containing (CBD) products) in the past year. Based on our prior experience as well as the experience of others, we expect 50% to have neuropathic pain and 50% to have past-year cannabis use after excluding frequent cannabis users.^9,40,61^

The treatment duration will be 8 weeks. Studies of cannabis for the improvement of neuropathic pain in other diseases have ranged in duration from 2 to 26 weeks. Another important component of chronic pain in SCD is chronic inflammation. Changes in inflammatory markers can also take weeks to occur, in studies of acute infections markers of inflammation such as CRP can take up to 6 weeks to normalize.62 Therefore, a study aimed at improving chronic pain in SCD or reducing inflammation should be done over weeks to months. We have chosen 8 weeks which we expect will be long enough to detect efficacy in pain and inflammatory outcomes and identify adverse effects.

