## 9.2 Sample Size Determination

In a study examining the responsiveness of PROMIS pain impact to changes in chronic pain patients who stated pain was a “little better” had an average increase of 1.8 point with a SD of 6.6 points and “much better” was associated with an average increase of 6.8 points with a SD of 6.5 points.^65^  Based on this we have chosen a change of 5 points as representing a clinically meaningful improvement in chronic pain, with an estimated a SD of 6.5 points. With a sample size of 28 patients (56 total) in each group we will have 80% power to detect a difference of 5 points in change between two groups in pain impact score from baseline at a two-sided 0.05 significance level.

We have a strong track record of following subjects with chronic pain, opioid use, and SCD in ourprior SCD studies have achieved 85-100% retention at 6 months. In our pilot trial we approached 27 patients to enroll 6 on study, we therefore estimate if we approach 280 patients, we can enroll 70. We conservatively estimate a 20% attrition rate, so we will aim to approach 280 patients to enroll 70 to ensure 56 participants completing the study.

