### 9.4.7 Sub-Group Analyses

Exploratory secondary analysis will be done examining patients with neuropathic pain only, and other pain types only, and patients who were cannabinoid naïve vs previous cannabinoid users, though these may be underpowered.

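### The subgroup plan tests each pain-type and prior-use subgroup separately and never compares the effect between them, so at the planned 5-point effect a uniform benefit gives one significant and one non-significant half in about 50% of trials

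*Protocol*

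**What the plan says.** The exploratory row of the table in section 3 reads "Analysis as above repeated examining patients with neuropathic pain only, and other pain types only", extends the same repetition to cannabinoid-naïve patients versus previous users, and adds that these analyses may be underpowered. Section 9.4.7 says "Exploratory secondary analysis will be done examining patients with neuropathic pain only, and other pain types only", and closes with "cannabinoid naïve vs previous cannabinoid users, though these may be underpowered".

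The analysis being repeated is defined in section 9.4.2: a rank-sum comparison between arms of change from baseline to end of study.

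Three other places touch the same factors or could be taken to supply a comparison:

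- Section 4.2 stratifies the 1:1 randomisation by neuropathic pain and by past-year cannabinoid use, and expects 50% of patients in each category.
- Sections 9.4.2 and 9.4.3 plan a backward stepwise regression to find covariates associated with the outcomes.
- Section 9.4.5 enters the two factors into models if they differ between the arms.

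The regressions are a covariate search and an adjustment for imbalance. Neither contains a treatment-by-subgroup term.

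**The concern.** Splitting a trial by pain type or prior use mainly informs on whether the drug's effect differs between the parts. Two separate tests, each against no effect, do not answer that. A significant result in one half and a non-significant result in the other is compatible with identical effects. When power per half is moderate, it is a common outcome.

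The protocol's warning about power points to missed effects within a subgroup. It does not tell the reader that the same low power makes a uniform effect look specific to one subgroup. The risk is a statement such as: works in neuropathic pain, does not work in other pain. The stated method readily produces that pattern and offers nothing to check it against.

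**Working it through.** **Inputs.** Section 9.2: difference in change of 5 points, "with an estimated a SD of 6.5 points", two-sided 0.05, 28 completers per arm, 70 enrolled. Section 4.2: 1:1 allocation, 50% with neuropathic pain. Section 9.4.2: rank-sum test.

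**1. The plan's own figure.** Section 9.2 says "With a sample size of 28 patients (56 total) in each group we will have 80% power to detect a difference of 5 points".

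- Normal approximation: n = 2 × (1.96 + 0.8416)² × (6.5/5)² = 26.5, so 27 per arm.
- The t-test needs 27.5, so 28. Its power at 28 per arm is 0.807.
- Attrition: 56/(1 − 0.20) = 70.

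The stated sample size reproduces.

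**2. Power in one half.** With 28 per arm split equally there are 14 per arm per half.

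- Normal approximation: SE = 6.5 × √(2/14) = 2.457, and Φ(5/2.457 − 1.96) = Φ(0.075) = 0.53.
- t-test: 0.50.
- Rank-sum, simulated: 0.455 (3,000 trials, normal data, 7 per arm in each of the four strata).

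**3. Chance of a split result when the effect is the same in both halves.** The halves are independent, so P(exactly one significant) = 2p(1 − p).

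- Normal approximation: 2 × 0.53 × 0.47 = 0.498.
- t-test: 2 × 0.50 × 0.50 = 0.500.
- Rank-sum, counted directly in the simulation: 0.497.

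In the same simulation a contrast of the two within-half effects, tested at 0.05, rejected in 0.049 of trials. The overall comparison was significant in 0.781 of trials, and it was significant together with a split on pain type in 0.451. Among trials with a significant overall result the split therefore appeared in 0.451/0.781 = 58%.

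**4. Dependence on the true effect** (t-test, 14 per arm per half). The values 1.8 and 6.8 are the average changes that section 9.2 cites for patients who felt a little better and much better. The values 2.5, 3.5 and 7.5 are assumptions to show the range.

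| Uniform effect (points) | Power per half | Exactly one half significant |
| --- | --- | --- |
| 1.8 | 0.109 | 0.19 |
| 2.5 | 0.165 | 0.28 |
| 3.5 | 0.279 | 0.40 |
| 5 | 0.500 | 0.50 |
| 6.8 | 0.759 | 0.37 |
| 7.5 | 0.836 | 0.27 |

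For equal halves 2p(1 − p) cannot exceed 0.50, so the planned effect sits at the maximum.

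**5. Dependence on the split and the number analysed** (5-point effect). A 40/60 split gives 0.51 and a 30/70 split 0.56. If all 70 are analysed (17.5 per arm per half) the figure is 0.47 to 0.48.

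**6. Precision of the missing contrast.** It is the difference of two within-half differences, so SE = 6.5 × √(4/14) = 3.47 points.

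- 95% CI half-width: 1.96 × 3.47 = 6.8 points.
- Difference in effects detectable with 80% power: (1.96 + 0.8416) × 3.47 = 9.7 points.

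**The case against.** **The analysis plan may supply the contrast.** The protocol need not give the model for an exploratory analysis, and an unseen analysis plan may add an interaction. That stands as far as it goes. But section 3 does not leave the method open: it says the main analysis is repeated in each subgroup. The point concerns that stated method.

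**The protocol never asks whether effects differ.** Section 9.1 contains no hypothesis of effect modification, and section 3 justifies the subgroups by saying the drug may act on each pain type. Within-subgroup results are a legitimate description, so they should stay. The protocol also nowhere says it will infer a difference from one significant and one non-significant test. A reader might infer that it plans to do so; the text does not support that.

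**The caveats are already there.** The analyses are labelled exploratory and possibly underpowered. This discourages reading a non-significant half as no effect, and it keeps the point minor. It does not provide the comparison.

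**The 50% can be over-read in two ways.** A reader might take it as unconditional; the table in the working shows that it is not. A reader might also apply it directly to prior use. The 50% expectation in section 4.2 is for past-year use, whereas sections 3 and 9.4.7 contrast naïve patients with previous users. Someone who last used cannabis two years ago is neither naïve nor in the past-year stratum, so the size of those groups is unknown.

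**The contrast itself is weak.** True: it has 80% power only for a difference of 9.7 points, nearly twice the planned effect. Its value is that the interval shows how little the trial can say about differences between subgroups.

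**Conclusion.** The point holds at minor severity. The protocol fixes separate within-subgroup tests and names no comparison of effects between subgroups. For pain type at the planned 5-point effect, a uniform effect yields exactly one significant half in about 50% of trials, against about 5% for an interaction test. For uniform effects of 1.8 to 7.5 points the range is about 19% to 50%, still several times 5%.

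This rests on SD 6.5, 56 completers, an equal pain-type split, approximately normal changes and a two-sided 0.05 reading of each half. The prior-use figure is similar only if previous users are the past-year stratum.

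A reader might infer that a false subgroup pattern would narrow the population of the phase III trial mentioned in section 2.3.3. That section ties the later proposal to efficacy in people with sickle cell disease and says nothing of selecting patients by subgroup, so such harm is possible but is not something the documents plan.

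**What to change.** In sections 3 and 9.4.7:

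- Keep the exploratory label and the within-subgroup effects, reported with 95% CIs.
- Add one treatment-by-subgroup contrast per factor on week-8 change in PROMIS pain impact. Section 9.4.1 assumes non-normal data, so use either a model with treatment, factor and their interaction with robust or permutation inference, or the difference between the within-subgroup Hodges-Lehmann shifts.
- Report the contrast as an estimate with its 95% CI, and base any statement that the effect differs by subgroup on it alone.
- Define previous cannabinoid user so that it matches the past-year stratification factor, or state that the two are deliberately different.

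The cost is a few lines of text and two extra analyses, with no added patients, visits or data. The downside is imprecision: with a 95% CI of about ±6.8 points the contrast will usually be inconclusive, and the report should say so.

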# 4 Study Design

## 4.1 Overall Design

Randomized, placebo-controlled, double masked, study of twice daily dronabinol given at a patient-optimized dose for 8 weeks. Participants will be titrated to optimized individual dose during the first week and continue at that dose for the remaining 8 weeks.  Randomization will be stratified by presence/absence of neuropathic pain and by history of cannabis use(yes/no) in blocks of four). Visits will occur every 2 weeks. Primary outcome is a difference in differences analysis of pain impact from baseline to 8 weeks compared between patients on dronabinol and on placebo. 

## 4.2 Scientific Rationale for Study Design

People with sickle cell disease (SCD) have chronic pain from multiple sources^2,3,15^ Inflammation is a driver of pain, end organ damage and early mortality in SCD.^16^ Tetrahydrocannabinol (THC) is a partial agonist for cannabinoid receptors (CB1 and CB2), and has been shown to be effective for the treatment of chronic pain and neuropathic pain in conditions such as cancer and multiple sclerosis.^6,17,18^ There is also evidence from murine models of SCD that CB1 agonists can reduce signs of chronic and neuropathic pain as well as inflammatory cytokines that are important in pain development in SCD.^3,4,19^ The proposed research is built on the scientific premise that dronabinol, an FDA-approved synthetic THC medication may treat chronic pain in SCD and reduce inflammation, and therefore is a promising agent for either the treatment of chronic pain or for treatment of the disease directly through reduction of inflammation.

Randomization will be done 1:1 to dronabinol or placebo in blocks of four, stratified by pain type (neuropathic or not) and past-year cannabinoid use (yes or no). Randomization will be done by the pharmacy. Neuropathic pain will be defined by LANSS score >12. Past-year cannabis use will be defined by self-report of any cannabinoid use (medical, illicit, or cannabidiol containing (CBD) products) in the past year. Based on our prior experience as well as the experience of others, we expect 50% to have neuropathic pain and 50% to have past-year cannabis use after excluding frequent cannabis users.^9,40,61^

The treatment duration will be 8 weeks. Studies of cannabis for the improvement of neuropathic pain in other diseases have ranged in duration from 2 to 26 weeks. Another important component of chronic pain in SCD is chronic inflammation. Changes in inflammatory markers can also take weeks to occur, in studies of acute infections markers of inflammation such as CRP can take up to 6 weeks to normalize.62 Therefore, a study aimed at improving chronic pain in SCD or reducing inflammation should be done over weeks to months. We have chosen 8 weeks which we expect will be long enough to detect efficacy in pain and inflammatory outcomes and identify adverse effects.

In a previous pilot study with a cross over study design ability to mask dronabinol was examined as other cannabinoid studies have shown it is difficult to mask psychoactive substances.^55^ Participants were asked if they thought they were receiving dronabinol or placebo at the end of each treatment period and again at the end of the study.  At the end of the first treatment phase, 4/6 (66%) guessed correctly, however at the end of the second treatment phase all 6 guessed correctly. This suggests that dronabinol can be masked on first exposure to drug or placebo, but the crossover design interferes with ability to mask. Dronabinol masking was not feasible during the second phase of the crossover, therefore this trial includes a placebo arm for does not include a crossover design.  

## 4.3 Justification for Dose

Dronabinol is an FDA approved drug with a good safety profile, known pharmacokinetics, and an oral formulation which is easily mimicked in a placebo formulation. Dosing. Dronabinol will be dosed twice daily. Dronabinol is eliminated in a biphasic manner, with an initial half-life of 4 hours and a terminal half-life of 25 to 36 hours.^6,50^ Decision to use twice daily dosing at an individualized dose is based both on the biphasic half-life and the dosing recommendations for appetite stimulation for which it is FDA approved. Dose titration. The dose of dronabinol will be individualized for each participant during the first week of treatment, from a minimum of 5 mg twice daily to a maximum of 10 mg twice daily. The initial dose for all participants will be 5 mg twice daily.,If it is well tolerated the dose will be increased to 10 mg twice daily. If they do not experience adverse effects, the final dose will be 10 mg twice daily. Placebo capsules will be labelled as 5.0 mg containing matching methylcellulose containing capsules.  As the study will be double-masked, dose optimization will be completed during the placebo arm as above.

Initial study doses ranged from 2.5mg twice daily to 10mg twice daily given in 2.5mg containing capsules. However, 2.5 mg capsules are no longer manufactured and only 5mg capsules are available, so the study has been modified to use 5mg capsules in doses range from 5 to 10 mg twice daily.

## 4.4 End of Study Definition

A participant is considered to have completed the study if he or she has completed all phases of the study including the last visit or the last scheduled procedure shown in the Schedule of Activities (SoA), Section 1.3

# 5 Study Population

## 5.1 Inclusion Criteria

| - Sickle cell disease (all genotypes) - Age >18 - Significant pain impact as defined by ASCQ-Me Pain impact score <60 - Chronic pain as defined by self reported daily or near daily pain in the past 6 months - If on a SCD modifying therapy (hydroxyurea, regular blood transfusions, L-glutamine, voxelotor, crizanlizumab), on stable dose for at least 3 months - If using opioids for pain at home, on stable dose for at least 3 months - Urine toxicology negative for cannabinoids at least 30 days before randomization |
| --- |

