| **Study Population:** | - Age >18 years - Clinical diagnosis of SCD (HbSS, HbSC, HbSβ+; Thal, HbSβ0Thal, HbS variants) - Baseline score of 60 or lower on the ASCQ-Me 7-day pain interference domain - If on a SCD modifying therapy (hydroxyurea, regular blood transfusions, L-glutamine, voxelotor, crizanlizumab), on stable dose for at least 3 months - If using opioids for pain at home, on stable dose for at least 3 months - One urine toxicology negative for cannabinoids within 30 days of randomization - No known intolerance to dronabinol, or marijuana - No history of psychotic episode, psychosis, or active suicidality - No contraindication to dronabinol with attention to potential side effects, concurrent medications/substances, and concurrent medical problems, as evaluated by a physician - Willing to abstain from cannabis, medical and illicit, during study weeks 1 through 8 - Not pregnant or nursing - If a woman capable of becoming pregnant, willing to use a medically accepted form of birth control for the duration of study participation.  Accepted forms include oral contraception, medroxyprogesterone, contraceptive implants or patch, surgical sterilization, total abstinence. - Able to consent for research - Daily cannabis use - Diagnosis of active substance use disorder |
| **Phase:** | 2 |
| **Description of Sites/Facilities Enrolling Participants:** |  |
| **Description of Study Intervention:** | Dronabinol or matching placebo |
| **Study Duration:** | 48 months |
| **Participant Duration:** | 8 weeks |

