Concomitant use of other drugs that cause dizziness, confusion, sedation, or somnolence such as CNS depressants may increase this effect (e.g., barbiturates, benzodiazepines, ethanol, lithium, opioids, buspirone, scopolamine, antihistamines, tricyclic antidepressants, other anticholinergic agents, muscle relaxants). Inform patients not to operate motor vehicles or other dangerous machinery until they are reasonably certain that MARINOL does not affect them adversely.

Concomitant use of other drugs that cause dizziness, confusion, sedation, or somnolence such as Central Nervous System (CNS) depressants may increase this effect (e.g., barbiturates (are central nervous system depressants medication that reduce the activity of nerves causing muscles to relax), benzodiazepines (which is central nervous system depressants medication that causes tiredness and are used to treat anxiety disorders, nervousness, panic disorders, muscle spasms, seizures, sleeplessness etc), ethanol, lithium, opioids, buspirone, scopolamine, antihistamines, tricyclic antidepressants, other anticholinergic agents, muscle relaxants).

Psychiatric risk potential:

Though the case reports suggest the possibility of serious side effects, there is insufficient evidence to establish a causal association between dronabinol and psychiatric symptoms. Given the potential psychiatric risks and the FDA warning, and in order to protect participant safety, we have elected to exclude patients with current bipolar disorder with psychosis, or psychotic disorder; current suicidal ideation; past year suicide attempt; or past year psychiatric hospitalization. Psychiatric monitoring plans and criteria for treatment discontinuation are detailed below (sections E2a and E2b).

Dronabinol is pregnancy category C, and there are no adequate studies for determining infant risk when using varenicline during breastfeeding.

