## 5.2 Exclusion Criteria

| - Pregnant or breastfeeding - Unwilling to use acceptable birth control - Unable to consent for research - Unwilling to avoid other cannabis products - Daily cannabis use - History of psychotic episode, psychosis, or active suicidality - Diagnosis of substance use disorder - Severe cardiovascular disease (MI, PTCA, unstable angina, CABG, and/or serious arrhythmia in the previous 6 months |
| --- |

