## 5.4 Screen Failures

Screen failures who fail due to positive urine test for cannabinoids may rescreen up to 3 times at least 2 weeks from date of last screen failure.

Screen failures who fail due to lack of chronic pain or insufficient pain impact score may rescreen in 3 months from date of screen failure.

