# 8 Study Assessments and Procedures

## 8.1 Efficacy Assessments

Informed consent will be obtained prior to screening activities. Screening may take multiple visits but must be completed within 30 days of obtaining informed consent. The following assessments will be completed:

- Written Informed consent
- Demographics
- Medical history - Including SCD type, SCD related problems, other medical problems, psychiatric and substance use history, description of pain and pain treatment
- Weight
- Vital Signs
- Review of current and past medications
- Pregnancy test - For women of child bearing potential Urine or serum.
- Urine test for cannabinoids
- Physical exam
- Baseline Patient Reported Outcomes (ASCQ-Me survey domains for pain impact, emotional impact, social impact, stiffness, and sleep, PROMIS domains for pain impact, neuropathic pain, nociceptive pain, cognitive function, gastrointestinal distress and anxiety. LANSS, PQ-B, C-SSRS)

Data will be collected from five sources: 1) Validated patient reported outcome surveys at baseline, and weeks 4 and weeks 8; 2) Timeline Follow-Back for hospital utilization use at research visits at weeks 4 and 8; 3) medical interview and physical examination at screening, weeks 4 and weeks 8; 4) laboratory markers of inflammation including IL1b, IL4, IL6, IL10, VCAM-1 and TNFα, tryptase, and substance P at baseline, weeks 4 and weeks 8 5) urine toxicology tests at baseline and weeks 4 and weeks 8, 6) safety laboratory tests of renal function, liver function, complete blood count and reticulocytes and pregnancy at screening and at weeks 4 and weeks 8;

In-person screening research interview, screening medical interview and physical examination data will be recorded on paper data collection instruments that identify participants only by unique study ID number. Patient reported outcome surveys will be performed on an I-Pad and entered automatically into REDCap. Data will be entered into a password-protected, encrypted web-based REDCap database, and paper documents will be filed in a locked cabinet.

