Urine toxicology tests will be performed at baseline and blood tests for cannabinoids at weeks 4 and weeks 8. Specimens will be labeled with the name of the research study, the date and time of collection, and the specimen number; no names or other identifying information will be used. The specimen number will be generated using the subject’s study ID number, the letters UT (to denote urine toxicology test), and the visit number. The laboratory will run toxicology tests for THC, methadone, opiates, cocaine, barbiturates, PCP, amphetamines, alcohol, and benzodiazepines on each specimen. The laboratory results will be available to [name] and the study assistant via the HIPAA compliant, encrypted, password protected clinical information system. They will not be reviewed until after the subject has completed the study to protect the masking.

We will conduct a blood test at screening and at weeks 4 and 8.  Laboratory markers of inflammation including IL1b, IL4, IL6, IL10, VCAM-1 and TNFα, tryptase, and substance P and safety laboratory tests of renal function, liver function, complete blood count and reticulocytes and pregnancy at screening and at weeks 4 and 8.

Assessments at weeks 2 and 6 are safety assessments only which consist of self reported adverse events, the PQ-B and the CSSR. These visits may be completed as in person or telemedicine visits.

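### The synopsis, the risk section and section 5 state different eligibility rules, including opposite limits on the age of the cannabinoid-negative urine sample

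*Protocol*

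**What the plan says.** Eligibility is stated in three places in the protocol.

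- **Urine test.** Section 5.1 (Inclusion Criteria): "Urine toxicology negative for cannabinoids at least 30 days before randomization". Section 1.1 (Synopsis, Study Population): "One urine toxicology negative for cannabinoids within 30 days of randomization".
- **Screening procedure.** Section 8.1 lists a urine cannabinoid test among the post-consent screening assessments and says: "Screening may take multiple visits but must be completed within 30 days of obtaining informed consent". Under section 5.4, a person who fails on a positive urine "may rescreen up to 3 times at least 2 weeks from date of last screen failure". Section 8.1 adds: "Urine toxicology tests will be performed at baseline and blood tests for cannabinoids at weeks 4 and weeks 8".
- **Psychiatric exclusions.** Section 2.3.1 says that, for participants' safety, the trial excludes psychotic disorder (including bipolar disorder with psychosis), current suicidal ideation, and "past year suicide attempt; or past year psychiatric hospitalization". Section 5.2 has one psychiatric item apart from substance use disorder: "History of psychotic episode, psychosis, or active suicidality". The synopsis carries the same item, worded as a negative.
- **Intolerance and contraindication.** The synopsis requires "No known intolerance to dronabinol, or marijuana" and a physician's judgement that dronabinol is not contraindicated. Neither is in 5.1 or 5.2.

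**The concern.** A negative urine before randomization is the only objective check on earlier cannabinoid use. The synopsis asks for abstinence in weeks 1 to 8 and section 5.3 during the study period, and the cannabinoid blood tests come at weeks 4 and 8. The primary outcome is change from baseline, so it matters whether the baseline is recorded in someone who has recently used cannabinoids. A criterion that sets only a minimum sample age gives no information on that.

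On safety, section 2.3.1 names worsening psychiatric symptoms as a serious risk of dronabinol and offers its exclusions as the protection. If the formal exclusion list is narrower, it can admit people whom the risk assessment takes to be excluded.

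There is also a practical consequence. With two incompatible rules in force, a monitor cannot decide whether a given enrolment was an eligibility deviation.

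**Working it through.** No stated figure has to be reproduced. The check compares the texts and intersects the two urine rules.

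**1. Urine window.** Let *a* be the age of the negative sample in days at randomization.

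- Synopsis: 0 ≤ *a* ≤ 30.
- Section 5.1, read literally: *a* ≥ 30, with no upper limit.
- Both together: *a* = 30 only.

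A sample 10 days old passes the synopsis and fails 5.1. A sample 45 days old does the reverse.

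**2. Which rule fits the rest of the protocol.**

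- Section 8.1 gives 30 days from consent to the end of screening. If randomization fell inside that period, a post-consent sample could satisfy 5.1 only if taken on the day of consent, with randomization on day 30. The protocol sets no limit between the end of screening and randomization, so this shows a poor fit and not an impossibility.
- Section 5.4 allows rescreening 14 days after a positive test. If the rescreen sample is the qualifying one, 5.1 would put randomization at least 14 + 30 = 44 days after the failed screen. The synopsis rule adds no wait beyond the 14 days.

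Both sections sit more easily with the synopsis, so 5.1 may be a slip. Nothing in the protocol says so.

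**3. Whether the baseline urine closes the gap.** Section 6.3 withholds from the study team only toxicology results obtained after randomization, which leaves the baseline result usable. Section 8.1, directly after describing the baseline urine and the later blood tests, says the laboratory results are not looked at until the participant has finished the study. The two sections disagree, so the baseline sample cannot be counted on as an eligibility check.

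**4. Risk section and synopsis against section 5.**

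| Item | Where stated | In 5.1 or 5.2? |
| --- | --- | --- |
| Psychotic disorder, including bipolar disorder with psychosis | 2.3.1 (current) | Yes, and more broadly (history) |
| Current suicidal ideation | 2.3.1 | Roughly, as active suicidality |
| Suicide attempt in past year | 2.3.1 | Not named; covered only if the opening words of the 5.2 item also govern active suicidality |
| Psychiatric hospitalization in past year | 2.3.1 | No |
| Intolerance to dronabinol or marijuana | Synopsis | No |
| Contraindication judged by a physician | Synopsis | No |
| ASCQ-Me pain score | Synopsis: 60 or lower | Differs: below 60 |
| Substance use disorder | Synopsis: active | Differs: any diagnosis |

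The criteria for chronic pain and severe cardiovascular disease run the other way: they are in section 5 and not in the synopsis.

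**The case against.** The strongest reply is that the screening procedure already does what 5.1 fails to say. Section 8.1 places a urine cannabinoid test after consent, and section 5.4 treats a positive result as a screen failure. Someone with an old negative sample who is still using would probably be caught. This stands as mitigation. It does not remove the contradiction, because neither section says how close to randomization the test must be, and the status of the baseline result is itself in dispute between 6.3 and 8.1.

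It is also fair to say that the synopsis rule does not prove abstinence at randomization. A person negative on day -29 who then uses cannabis still meets it. An upper limit reduces the uncertainty without removing it.

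On the psychiatric items, section 8.2 requires thorough medical and psychiatric screening with a psychosis questionnaire and a suicidality scale, and both are repeated during the study. That is a real safeguard. But section 8.2 refers for the criteria to a Human Subjects section that does not exist under that name, and the instruments do not replace a stated exclusion for a past-year hospitalization.

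A reader might infer more than the documents support:

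- *That half the sample could be recent users.* The expected 50% is self-reported use of any cannabinoid, including CBD products, at any time in the past year. It does not measure recent THC use.
- *That the treatment comparison would be distorted by cannabis withdrawal in the placebo arm.* Section 5.2 excludes daily use, any substance use disorder diagnosis and unwillingness to avoid cannabis. No figure in the protocol supports such an effect in the remaining population.
- *That the 5.1 sample would usually pre-date consent.* This does not follow, since the interval from screening to randomization is not limited.

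**Conclusion.** The eligibility statements contradict each other and are wrong as they stand. The urine rules in 5.1 and the synopsis share a single day. Of the psychiatric exclusions in 2.3.1, past-year hospitalization is plainly missing from 5.2 and past-year suicide attempt is not named; the others are covered fully or roughly. Two synopsis criteria are missing from section 5, and two more differ in their cut-off or scope.

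The size is the number of conflicting criteria. The documents give no basis for a count of affected participants or for a bias in points on the primary outcome. The primary test and the planned 28 per group, 56 completers and 70 enrolled do not depend on this point. The conclusion assumes that 5.1 is read as written; if it was meant to match the synopsis, the defect is one of drafting, but it still needs correcting because the formal list is the natural source for a screening form.

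**What to change.** Merge the synopsis, 2.3.1, 5.1 and 5.2 into one eligibility list and have every section refer to it.

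- State the urine criterion once, as a window with an explicit upper limit on sample age relative to randomization, consistent with the screening period in 8.1 and the rescreen interval in 5.4.
- Reconcile 6.3 and 8.1 on whether the baseline toxicology result may be seen before randomization.
- Have the investigators settle which psychiatric, intolerance and contraindication exclusions apply, so that the risk assessment and the screening list match. Which clinical rule is right is for them to decide.
- Align the ASCQ-Me cut-off and the scope of substance use disorder, carry the chronic pain and cardiovascular criteria into the synopsis, and correct the reference in 8.2.

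The cost is a protocol amendment and an updated screening form, with possibly a few more repeat urine tests or screen failures. Section 5.4 already provides for repeat testing.
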